#### Primary outcome measurements

Primary outcome measure in this study is the effectiveness of early assisted discharge compared to usual care expressed by the change on the Clinical COPD Questionnaire (CCQ) [38] between the third day of admission (T1) and the last day of supervised treatment (T2 = day 7). The CCQ is a disease specific, ten-item questionnaire that calculates an overall score and three domain scores: symptoms, functional state and emotional state. All items are scored on a seven point scale with 0 representing the best possible score and 6 representing the worst possible score [38]. In this study the version with a 24-hour recall period is used, reflecting the health status of the past 24 hours. The CCQ is responsive to change [38] and a study in patients admitted to the hospital with an acute exacerbation of COPD, indicated that the minimal clinical important difference (MCID) of the CCQ is 0.4 [40].

#### Secondary outcome measurements

Main secondary outcome measurement of the study is the cost-effectiveness. This will be discussed in the economic evaluation section. The following other secondary measurements will be performed. These correspond with the secondary research questions from the last paragraph of the introduction:

1. Long-term effectiveness, measured with the CCQ change over the time points from day 1 to the end of the follow-up period (T4).

2. Number of treatment failures.

3. Number of readmissions to hospital and time to readmission during the three months follow-up period.

4. Mortality and time to death during the three months follow-up.

5. Generic health related quality of life, measured with the EuroQol (EQ-5D) 5D [41]. The EQ-5D will also be used to calculate quality adjusted life year (QALYs), discussed in the economic evaluation section.

6. Effects on primary informal caregiver burden measured by the Caregiver Strain Index [42].

7. Patient and primary informal caregiver satisfaction with the program. We use a translated version of the satisfaction questionnaire used by Ojoo et al. [24] and extended it with additional questions.

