### Treatment protocol day 1-3 and day 4-7

The treatment protocol during the seven days of supervised treatment can be divided in the treatment before randomisation and the treatment after randomisation.

During the first three days of the treatment all patients receive usual care. The pharmacological part of this treatment consists of systemic corticosteroids (10 days in total, first 3 days 50 mg of oral or intravenous prednisolone or other corticosteroid with an equivalent dose, following 7 days of 30 mg oral prednisolone or other corticosteroid with an equivalent dose), nebulised bronchodilators (ipratropium 500 μg/salbutamol 2.5 mg, 4-6 times per day), sub cutaneous thrombosis prophylaxis, stomach protection - because of the high dosage of corticosteroids - and, if necessary, oxygen therapy. Antibiotics are prescribed if patients meet any of the following criteria: increase of the amount of mucus, mucus purulence or CRP > 50 for which no other cause can be determined. First choice of antibiotics is co-amoxiclav. However, if previous mucus cultures show sensitivity for different antibiotics, or patients are allergic, different antibiotics can be prescribed. Antibiotics are prescribed for at least 7 days.

Non-pharmacologic usual care consists of physiotherapy for all patients and dietary advice upon indication [39]. The physiotherapist instructs the patient in breathing and coughing techniques and reactivation. A standardised (additional) written instruction was developed ensuring identical instruction in the participating hospitals. Dietary advice is indicated in case of a Body Mass Index ≤ 21 or 10% unintended weight loss in the six months prior to admission [39].

After randomisation systemic corticosteroids are continued and patients start with pressure metered dose inhaled medication via spacer (at least an β_2_-antagonist or anticolinergic with inhaled glucocorticosteroid). Patients receive inhalation instruction on the day before starting with these inhalations. Patients already using nebulised inhalation medication prior to admission, may continue this after randomisation.

The physiotherapist instructs patients to follow the written instructions at home and dietary consultation is continued as in usual care and at the dietician's judgement.

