### Data collection

Data are collected on five time points: on the first day of admission (T0), on the third day of admission (randomisation, T1), at the end of the supervised treatment (day 7, T2) and one month (T3) and three months after randomisation (T4).

We use self-administered questionnaires and cost diaries to obtain data. The questionnaires are administered when supervision is available. Cost diaries are supplied at two time points (T2 and T3) for the up coming period, collected at the end of each follow up period and if necessary completed under supervision.

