### Effect evaluation

Table 2 provides an overview of the measures of the effect evaluation and the economic evaluation, and at which time point the measurements are performed.

**Table 2 T2:** Overview of measurements per time point

Measurement	T0	T1	T2	T3	T4
					

Demographic characteristics	x				

Smoking	x				

Body Mass Index	x				

Living situation	x				

Comorbidity	x				

Coping style (UCL)		x			

Medical treatment prior to admission	x				

Exacerbation severity	x				

Indication for admission	x				

Clinical COPD Questionnaire (CCQ)	x	x	x		x

EuroQol 5D (EQ-5D)		x	x		x

Satisfaction					

patient satisfaction			x		x

primary caregiver satisfaction			x		x

Caregiver Strain Index			x		x

Treatment Failures			x		

Readmissions					x

Mortality					x

Cost diary			x (IG)	x	x

Discrete Choice Experiment				x	

Lung function testing					x

6 Minute Walking Distance					x

T0 = baseline; T1 = randomisation; T2 = end of supervised treatment; T3 = follow up 1; T4 = follow up 2; IG = intervention group only

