### Economic evaluation

In accordance with the broad international consensus that economic evaluations should be conducted from a societal perspective [45] this cost-effectiveness analysis will include all costs, irrespective of who actually bears them.

All direct health care and non-health care costs as well as the costs of productivity losses of patient and caregiver within the three months after randomisation will be taken into account.

The following types of resource use will be recorded to calculate direct health care costs: number and length of hospital admissions and readmissions, total amount of time of community nursing care (distinguished by nurse grade), number of visits to the emergency department, number of contacts with pulmonologist, other specialist physicians, general practitioner, respiratory nurse, dietician, physiotherapist, and social worker, number of ambulance rides and medication use. These will be recorded in cost diaries and obtained from hospital records. Costs of organisational arrangements of the early discharge scheme will also be included.

Direct non-health care costs primarily include paid and unpaid household help, including the time spent by the primary informal caregiver.

Indirect costs are costs of productivity losses. We record the days a patient is absent from paid work. We also ask informal caregivers to record the number of days off work due to caring for the patient. Costs are calculated by multiplying the volume of resource use (such as hospital days, physician visits, time spent by formal and informal caregivers) by a price per unit that includes total, not marginal costs.

In addition to the societal perspective, we will calculate the costs from the financial hospital perspective, the financial perspective of the organisation providing the home care and the perspective of the health care sector. This includes costs covered by the hospital budget, the budget of the homecare organisation and the health care sectors budget, respectively.

The principal health outcome measures in the economic evaluation are the number of patients with a clinically relevant improvement in CCQ between day of randomisation and day 7, and between day of randomisation and month 3, the change in CCQ score between day of randomisation and day 7 and day of randomisation and month 3, the number of QALYs randomisation and the end of the three-month follow-up period. The latter is calculated using the Dutch EQ-5D tariff [46].

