#### Primary outcome measure

The changes on the primary outcome measurement, the CCQ, will be analysed with the repeated measurements ANOVA technique. The dependent variable is the change in CCQ score from baseline (T1) to the end of the supervised treatment (T2). Treatment group is considered as independent variable and baseline CCQ score (T1) and centre of treatment are considered as covariates. Age, gender and severity of the disease will also be included in the model as covariates. If necessary, other covariates will be included in the model.

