#### Secondary outcomes measurements

All time-to-event outcomes (i.e. time to readmission and time to death) will be analysed using Kaplan-Meier curves and Cox Proportional Hazards regression model. Event rates (i.e. treatment failures, readmission rates and mortality rates) will be analysed using an appropriate model for count data (e.g. poisson regression or binomial regression)

Differences in outcomes defined as the mean change from baseline (e.g. long-term effectiveness, primary informal caregiver burden, patient- and primary informal caregiver satisfaction and quality of life) will be analysed using repeated measurements ANOVA.

Patient- and caregiver preference for place of treatment will be analysed using a logistic regression model.

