### Sample Size calculation

Primary outcome is the change in the CCQ score between baseline (day 3 of admission) and the end of the supervised treatment (day 7).

Before the start of the study, a preliminary sample size calculation for an independent samples t-test was performed based on the results of a pilot study, where the average CCQ decreased from 3.8 on the day of admission to 2.6 by the end of the supervised treatment The standard deviation of that change was 1.04. With a MCID of 0.4, the required Cohen's effect size d would be 0.385 [99]. For a risk of a type-I error of 5% (α = 0.05) and a risk of a type-II error 20% (1-β = 0.80), the required sample size was 214.

However, primary outcome measure in this study is the change in the CCQ score from the third day of admission and the end of the supervised treatment (day 7), which is likely to have a stronger correlation with the baseline score. Therefore, a new sample size calculation for ANCOVA was performed after 85 patients had been treated, without breaking the randomisation code. Taking into account the correlation between the baseline score and the change (r = 0.288), as well as the standard deviations measured in the trial (0.988 for the intervention group and 0.922 for the control group), the required effect size f is 0.22 and the sample size is 165.

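### Long-term CCQ effectiveness is defined from day 1, before randomisation, while the primary outcome and the three-month economic CCQ change start at randomisation (T1)

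*Protocol article*

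**What the plan says.** The time points are defined under Data collection: "on the first day of admission (T0), on the third day of admission (randomisation, T1" is day 3. Under the treatment protocol for days 1-3, "During the first three days of the treatment all patients receive usual care".

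Four places then fix, or depend on, the start of the CCQ change:

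- Secondary outcome measurements, item 1 (long-term effectiveness): "measured with the CCQ change over the time points from day 1 to the end of the follow-up period (T4".
- Data analysis, Primary outcome measure: "The dependent variable is the change in CCQ score from baseline (T1) to the end of the supervised treatment (T2". Primary outcome measurements and Sample Size calculation use the same start, day 3.
- Economic evaluation, principal health outcomes: "the change in CCQ score between day of randomisation and day 7 and day of randomisation and month 3".
- Data analysis, Secondary outcomes measurements: "Differences in outcomes defined as the mean change from baseline (e.g. long-term effectiveness, primary informal caregiver burden" and others are to go to repeated-measures ANOVA. This section does not say which time point is the baseline.

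The footnote to Table 2 reads "T0 = baseline; T1 = randomisation; T2 = end of supervised treatment". Table 2 schedules the CCQ at T0, T1, T2 and T4.

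**The concern.** The same questionnaire followed to the same three-month visit has two start points: T0 for the clinical long-term outcome and T1 for the economic one. The section that assigns the analysis refers only to baseline, a word that the article uses for T0 in one place and for T1 in others. An analyst could follow the text correctly and reach either version.

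Nothing that happens between T0 and T1 can be a treatment effect, because care is the same and allocation has not yet taken place. Including that interval brings no information on the contrast and may bring variance. It also makes each arm's reported change partly a product of selection: the randomisation criteria require respiratory complaints to have eased since day 1, so some improvement after T0 is a condition of entry. That part cancels between the arms, but it would enlarge the within-arm changes a reader sees.

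At stake are the precision of the answer to the first secondary research question, and whether the clinical and economic CCQ results at three months can be read together.

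**Working it through.** **1. Reproduce the article's own figures** (Sample Size calculation; two-sided 5% assumed, 80% power, 1:1, difference 0.4).

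- From admission: "The standard deviation of that change was 1.04". n per arm = 2(1.96 + 0.84)² × (1.04/0.4)² = 106.1, rounded up to 107, total 214. The stated 214 is reproduced.
- From T1: I read the trial SDs of 0.988 and 0.922 as SDs of the T1-T2 change. Pooled SD = √((0.988² + 0.922²)/2) = 0.956. Adjusted for the baseline score, residual SD = 0.956 × √(1 − 0.288²) = 0.915, so f = 0.2/0.915 = 0.219. This gives a total of 166 (164 with f rounded to 0.22), in line with the stated 165.

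**2. Compare start points like for like at day 7, both unadjusted.**

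- Variance ratio = (1.04/0.956)² = 1.18.
- Total N for 0.4: 214 from admission, 180 from T1.
- Power at N = 165, from Φ(0.4/(SD × √(2/82.5)) − 1.96): about 70% with SD 1.04 and 77% with SD 0.956. With covariate adjustment from T1 (0.915) it is 80%.

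The 1.04 comes from the pilot and the 0.956 from the trial, so part of the difference may lie between the samples.

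**3. Month 3.** The article gives no SD or correlation here. Assume equal SDs at T0, T1 and T4, with correlations r04 (T0 with T4) and r14 (T1 with T4). The variance of the change from T0 relative to that from T1 is (1 − r04)/(1 − r14):

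| r04 | r14 | ratio |
|---|---|---|
| 0.3 | 0.5 | 0.7/0.5 = 1.40 |
| 0.3 | 0.4 | 0.7/0.6 = 1.17 |
| 0.4 | 0.4 | 1.00 |
| 0.5 | 0.4 | 0.5/0.6 = 0.83 |

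These are illustrations, not limits; 0.4 and 0.6, for example, give 0.6/0.4 = 1.50. The ratio exceeds 1 whenever the later measurement, T1, correlates more strongly with T4 than T0 does.

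**4. Is the contrast biased?** Simulation: 20,000 runs, 82 per arm, SD 1, true effect −0.40 at T2 and T4, r04 = 0.3, r14 = 0.5.

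- T4 minus T0: mean −0.401, standard error 0.185.
- T4 minus T1: mean −0.399, standard error 0.156.

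The expected contrast is the same from either start; only the precision differs.

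**5. Does adjustment for T1 protect precision?** On the same scale, the variance of T4 adjusted for T1 is 1 − r14², against 2(1 − r04) for a raw change from T0. In the least favourable row of the table this is 1 − 0.16 = 0.84 against 2 × 0.5 = 1.00. Against T4 adjusted for T0 alone, the ratio (1 − r04²)/(1 − r14²) is 0.91/0.75 = 1.21 at 0.3/0.5 and 0.75/0.84 = 0.89 at 0.5/0.4. Adding T0 as a second covariate covers that last case.

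**The case against.** The strongest reply is that the between-arm comparison is sound from either start. Randomisation follows the T0-T1 interval, so recovery in that interval cancels in expectation. This stands, and it means that the clinical and economic definitions target the same expected difference.

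It can also be said that the article leans towards T1 as the analysis baseline. The primary analysis and the sample size section say so; EQ-5D is not measured at T0, so its change from baseline can only start at T1; and covariance analysis is planned for all outcomes. Following patients from admission is moreover a legitimate description of recovery, and model detail may sit in a fuller plan. This stands in part. It does not remove the explicit day-1 start in item 1 or the Table 2 footnote, which are statements and not omissions.

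Three stronger readings are tempting, and the document does not support them:

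- *The effect is diluted.* If T0 and T1 were entered as outcome occasions and an overall group effect were read as the treatment effect, a true 0.40 at T2 and T4 would average 0.40 × 2/4 = 0.20 over the four raw scores (simulated: −0.200), or 0.40 × 2/3 = 0.27 over changes from T0 at T1, T2 and T4. The text neither states nor excludes such an analysis.
- *Variance rises 29% and power falls from 80% to about 70%.* (1.04/0.915)² = 1.29 sets an unadjusted pilot SD against a covariate-adjusted trial SD, so it mixes the gain from adjustment with the start point.
- *The long-term result is certainly less precise.* With no month-3 correlations given, the direction is likely but can reverse.

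**Conclusion.** The point holds as an inconsistent baseline for one secondary outcome. Long-term CCQ change starts at T0 in its definition, the matching economic outcome starts at T1, and the analysis section's baseline can be read as either.

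The likely consequence is lost precision, not bias. At day 7 the only available figures suggest about 18% more variance from admission, or power of roughly 70% against 77% at N = 165. This assumes that the pilot and trial samples are comparable and that the trial SDs refer to the T1-T2 change. At month 3 the size is unknown: 0.83 to 1.40 over the tabulated assumptions, with values above 1 more plausible because T1 is closer in time to T4. The article makes no power claim for this outcome, and the primary analysis and sample size do not depend on it. It is worth correcting because the correction is nearly free.

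**What to change.** In Secondary outcome measurements, item 1, define long-term effectiveness as the between-group difference in CCQ at T4, adjusted for CCQ at T1. T2 may be an outcome occasion in the same repeated-measures model, provided that the T4 contrast is named as the result. T0 may be a further covariate or be reported descriptively. State that neither T0 nor T1 enters as an outcome occasion.

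Use T1 as the baseline for treatment comparisons throughout: say so in the analysis section for secondary outcomes, and relabel T0 in the Table 2 footnote, for instance as admission.

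The cost is wording only. The CCQ is already scheduled at T0, T1, T2 and T4, so no visit, questionnaire or sample size changes.

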#### Patient characteristics

Patients are characterised using the following variables: demographic factors (age, gender, socioeconomic status measured through level of education and income), smoking, Body Mass Index, living situation, comorbidity measured with the Charlson Comorbidity Index (CCI) [43], Coping Style measured with the Utrecht Coping List [44], medical treatment at home prior to the admission, severity of the exacerbation, indication for admission and finally severity of the disease are measured as well. In addition, severity of COPD is measured three months after admission at the end of the follow up period by performing lung function testing and a six minute walking test.

### Economic evaluation

In accordance with the broad international consensus that economic evaluations should be conducted from a societal perspective [45] this cost-effectiveness analysis will include all costs, irrespective of who actually bears them.

All direct health care and non-health care costs as well as the costs of productivity losses of patient and caregiver within the three months after randomisation will be taken into account.

The following types of resource use will be recorded to calculate direct health care costs: number and length of hospital admissions and readmissions, total amount of time of community nursing care (distinguished by nurse grade), number of visits to the emergency department, number of contacts with pulmonologist, other specialist physicians, general practitioner, respiratory nurse, dietician, physiotherapist, and social worker, number of ambulance rides and medication use. These will be recorded in cost diaries and obtained from hospital records. Costs of organisational arrangements of the early discharge scheme will also be included.

Direct non-health care costs primarily include paid and unpaid household help, including the time spent by the primary informal caregiver.

Indirect costs are costs of productivity losses. We record the days a patient is absent from paid work. We also ask informal caregivers to record the number of days off work due to caring for the patient. Costs are calculated by multiplying the volume of resource use (such as hospital days, physician visits, time spent by formal and informal caregivers) by a price per unit that includes total, not marginal costs.

In addition to the societal perspective, we will calculate the costs from the financial hospital perspective, the financial perspective of the organisation providing the home care and the perspective of the health care sector. This includes costs covered by the hospital budget, the budget of the homecare organisation and the health care sectors budget, respectively.

The principal health outcome measures in the economic evaluation are the number of patients with a clinically relevant improvement in CCQ between day of randomisation and day 7, and between day of randomisation and month 3, the change in CCQ score between day of randomisation and day 7 and day of randomisation and month 3, the number of QALYs randomisation and the end of the three-month follow-up period. The latter is calculated using the Dutch EQ-5D tariff [46].

Health outcomes will be related to cost outcomes. If one of the treatment options is more effective but also more costly, results will be presented as an incremental cost-effectiveness analysis: the additional cost per additional unit of health gain, which is calculated as the difference in mean costs between early discharge and usual inpatient hospital care divided by the in mean health effects.

### Data analysis

Data analysis will be performed according to the intention to treat principle. Data from patients who die, quit participation or are otherwise lost to follow up will be included in the analysis up until the point of drop out. Missing observations will be imputed or weighted appropriately.

All primary and secondary outcome measurements will be analysed using analysis of covariance. In order to control for dependency between the repeated measurements within one patient, and for the dependency between patients from the same hospital, multilevel analyses will be performed as well. We set the significance level at α = 0.05.

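### Data on readmission and death stop at drop-out, although hospital records are already consulted for readmissions in the costing

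*Protocol article*

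**What the plan says.** All references are to the protocol article.

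- **Data analysis.** The section opens with "Data analysis will be performed according to the intention to treat principle". It goes on to say that the data of those who "quit participation or are otherwise lost to follow up will be included in the analysis up until the point of drop out", and it treats deaths in the same way. It then adds: "Missing observations will be imputed or weighted appropriately". No outcome is exempted, and the article does not distinguish a patient who stops questionnaires from one who refuses any further use of records.
- **Secondary outcome measurements.** Item 3 is "Number of readmissions to hospital and time to readmission during the three months follow-up period". Item 4 is the corresponding outcome for death. The section on analysis of secondary outcomes assigns Kaplan-Meier curves and Cox regression to the times, and a count or binomial model to the rates.
- **Effect evaluation, Table 2** ("Overview of measurements per time point"). The rows for "Readmissions" and for mortality are each marked at T4 (month 3) only. "Treatment Failures" is marked at T2 (day 7).
- **Economic evaluation.** Hospital admissions and readmissions head the list of resource use over the three months after randomisation. On the source of these data it says: "These will be recorded in cost diaries and obtained from hospital records". Death is not on that list.

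**The concern.** Readmission and death can be established without the patient attending a visit or completing a form. A rule suited to questionnaire scores is here applied to events that can be looked up, and for readmissions the source is one the trial already uses.

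Treatment failure is defined differently in the two arms. Three-month readmission and mortality are therefore the safety outcomes defined alike in both. If patients who quit or are lost differ in risk from those who stay, and more so if drop-out differs between home and hospital care, censoring at drop-out biases the comparison. The arm that loses more high-risk patients looks better than it is.

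There is also a loose end between sections. Read on its own, the Economic evaluation would cost a readmission that occurs after drop-out but within three months. Under the Data analysis rule the same event falls outside the comparison of readmissions.

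**Working it through.** **The plan's figures.** The article states no drop-out rate, readmission rate or death rate, so there is no plan figure for this point to reproduce. The only figure borrowed is the revised sample size of 165 with 1:1 allocation, about 82 per arm. It reproduces closely:

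- pooled SD = √((0.988² + 0.922²)/2) = 0.956
- residual SD = 0.956 × √(1 − 0.288²) = 0.915
- f = 0.4/(2 × 0.915) = 0.219
- total of about 166, or 164 with f rounded to 0.22.

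**Illustration 1 (assumed inputs).** Drop-out is 10% in arm A and 20% in arm B. Three-month readmission risk is 30% in completers and 50% in drop-outs.

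| | Arm A | Arm B | B − A |
|---|---|---|---|
| True risk | 0.9×0.30 + 0.1×0.50 = 32% | 0.8×0.30 + 0.2×0.50 = 34% | +2 points |
| Kaplan-Meier, drop-outs censored very early | about 30% | about 30% | about 0 |
| Crude proportion of all randomised, no drop-out events counted | 0.9×0.30 = 27% | 0.8×0.30 = 24% | −3 points |

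Patients censored very early are out of the risk set before events occur, so the Kaplan-Meier estimate becomes the completers' risk. Later drop-out would keep some of their events and lose less. At most 0.1×0.50×82 ≈ 4 and 0.2×0.50×82 ≈ 8 readmissions go unseen.

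**Illustration 2 (assumed inputs).** True risk is 30% in both arms, and drop-out is 15% v 5%. Drop-outs carry k times the completers' risk. For drop-out proportion d, completers' risk = 0.30/(1 − d + d×k).

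- k = 1: completers 30% v 30%, difference 0. Crude 0.85×0.30 = 25.5% v 0.95×0.30 = 28.5%, difference −3.0 points.
- k = 2: completers 0.30/1.15 = 26.1% v 0.30/1.05 = 28.6%, difference −2.5 points. Crude 0.85×0.261 = 22.2% v 0.95×0.286 = 27.1%, difference −5.0 points (unrounded).

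**Equal drop-out.** With 10% drop-out in both arms and equal true risk, no spurious difference arises. With true risks of 36% v 26% and k = 2, completers show 0.36/1.1 − 0.26/1.1 = 9.1 points and the crude proportion 0.9×9.1 = 8.2 points, against a true 10.

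**Scale.** The standard error of a difference between two proportions near 33% with 82 per arm is √(2×0.33×0.67/82) ≈ 7 points. The biases above are smaller than the sampling error. Unlike sampling error, however, they have a direction, and most can be avoided by looking the events up.

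**The case against.** Several stronger readings are tempting, and the article does not support them.

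- **That readmission and death are recorded only at the month-3 visit.** Death before day 7 in both arms, and readmission before day 7 in the intervention arm, are captured at T2 as treatment failures. Cost diaries collected at T3 and T4, and hospital records, also pick up readmissions. The T4 mark can equally mean a cumulative count at the end of follow-up, since the time-to-event outcomes require dates.
- **That drop-outs leave the safety comparison.** They contribute until they drop out, and imputation or weighting is foreseen for what follows.
- **That the rule contradicts intention to treat.** Analysing patients as randomised and censoring them at loss is ordinary practice. It brings an assumption about drop-out, not a contradiction.
- **That the comparison would change sign.** In Illustration 1 the move from +2 to −3 points arises only if drop-outs stay in the denominator with no events. The article does not specify that estimator. Under early Kaplan-Meier censoring the difference shrinks to about zero.
- **That drop-outs are the patients who deteriorated.** This is plausible, but the article does not say it.

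It can also be argued that withdrawal categories belong in a full protocol or analysis plan that is not shown, and that the text does not forbid a records search after a missed visit. That limits the point but does not remove it: the article states a stopping rule for all outcomes and gives no exception. Imputation or weighting is no full substitute. Weighting relies on recorded data explaining drop-out, and imputing an event that can be looked up is inferior to looking it up.

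**Conclusion.** The point holds in a limited form. As written, data for patients who quit or are lost end at drop-out for every outcome. The records search used for costs is not extended to their readmissions, and their vital status is not provided for. Three-month readmission and mortality are therefore open to avoidable and possibly informative censoring.

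The size is unknown. Under the assumed inputs, the distortion of the readmission difference is about 2 points in Illustration 1 and 0 to 2.5 points in Illustration 2 where drop-outs are in effect excluded. It reaches 3 to 5 points where their events count as absent. It matters mainly when drop-out differs between arms or is related to deterioration. The sample size calculation is not affected. The change should be made because it is cheap and concerns the safety evidence, not because a material bias has been shown.

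**What to change.** 1. In the Data analysis section, separate stopping questionnaires, diaries or visits from withdrawing consent to the use of records.
2. For readmission, death and the time to each, follow every randomised patient to three months after randomisation. Use the hospital records already consulted for costs, plus a separate vital-status check, because the listed record items do not include death. Censor only at withdrawal of consent to record use or at three months; death itself ends follow-up for readmission.
3. State in Table 2 that the T4 entries for readmissions and mortality cover all events, with dates, from T1 to T4.
4. Keep imputation or weighting for what still cannot be ascertained.

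The cost is some rewording and a records and vital-status check for the drop-outs, and the consent must cover that use of records. Admissions to non-participating hospitals and deaths outside hospital may still be missed, and this limit should be reported.
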